### Procedure

Enrollment and intervention procedures will be self-guided. Individuals who register to start the *Daybreak* program generate a username and password, and they will then be asked if they are interested in participating in the project. For those affirming, they will then receive the full study description and be asked for active consent (clicking on a button). They will then be screened for eligibility by completing a Web-based survey, before being randomized. Those that are screened as ineligible are returned to the *Daybreak* on-boarding procedure (Multimedia Appendix 1) and notified of their ineligibility, and they are provided with relevant details of the crisis support services. Participants have unlimited access to their respective areas, and those randomized to *Daybreak* plus coaching can access a health coach (available from 7 AM to 7 PM local time Monday-Friday).

At 1, 3, and 6 months, participants will be emailed and texted a link to the follow-up survey. If they do not complete the survey, a repeat text message will be sent 1 week later. Following this, a research assistant (blind to group allocation) will call the participants to remind them to complete the survey on a maximum of 3 occasions and provide the link again via email or text message if requested during the call. At each wave, participants will be invited to enter their details for a prize draw to win an iPad 2. Participants do not have to complete the survey to enter the draw, but the link to the prize draw will be at the end of the surveys. The study received institutional ethics approval (2017-0855) and has been registered with the Australian and New Zealand Clinical Trials Registry trial number ACTRN12618000010291.

Recruitment will be conducted over 10 months from February to November 2018 or until the desired sample size is obtained. New registrants either directly download the *Daybreak* app from the App Store, or reach the Hello Sunday Morning website (where they are directed to download it) by searching Google, or by clicking from other websites such as healthdirect.gov or other health service directories, or by clicking through from the Hello Sunday Morning email newsletter.

### Sample Size

We are unaware of any prior studies using social networks for alcohol reduction, but for other behaviors, the reported changes are small but not significant [31].

**Figure 1 figure1:**
[figure not shown]
Flowchart of participants through the trial.

The effect sizes for Web-based SBI alcohol interventions are in the range *d*=0.3-0.4 at 6 months [19-21]. On the basis of a small estimated effect size of *f=* 0.10 (equivalent an effect size of *d*=0.2) at 6 months, with a correlation between repeated measures of *r*=0.5, we will require 60 people per group for the main analysis based on power of 0.80 and alpha set to *P*<.05. Given the interest in the effectiveness of interventions by gender and for those with probable dependence (assessed via the AUDIT), the objective will be to recruit approximately 60 people in the smallest cell(s). From demographic data [35] with about 50% of the *Daybreak* population likely to be in the probable dependence AUDIT category and 40% being male, to obtain about 60 people in this cell will require 300 people per study arm (600 in total). To allow for attrition, the target will be to recruit 467 per arm (N=934), with 35% lost to follow-up.

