**Methods:**

We will use a between groups randomized control design. New participants enrolling in the *Daybreak* program will be eligible to be randomized to receive either (1) the *Daybreak* program, including peer support plus behavioral experiments (these encourage and guide participants in developing new skills in the areas of mindfulness, connectedness, resilience, situational strategies, and health), or (2) the *Daybreak* program, including the same peer support plus behavioral experiments, but with online coaching support. We will recruit 467 people per group to detect an effect size of *f*=0.10. To be eligible, participants must be resident in Australia, aged ≥18 years, score ≥8 on the alcohol use disorders identification test (AUDIT), and not report prior treatment for cardiovascular disease.

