The benefits of including additional resources to support internet-based interventions are currently unclear. A meta-analysis of internet interventions for depression found a large effect size (*g*=0.78) [25], where all except one of the studies included therapist support. In contrast, a meta-analysis of self-guided internet interventions for depression reported a small effect size (*d*=0.28) [26]. However, a comparison of alcohol interventions found no significant difference between guided (effect size *g*=0.23) versus unguided (effect size *g*=0.20) interventions, although the authors note that this may be due to the small number of guided studies [19]. Nevertheless, benefits have been shown in improving alcohol outcomes (and other health behaviors) from using multiple modes of delivery such as text messages, drawing on theoretical models, and incorporating multiple behavioral change techniques [27,28].

Observational data show that a person’s social network can either increase or decrease their alcohol use [29]. Social networks now include those formed on the internet. These sites range from simple bulletin boards through to virtual lives, but typically allow users to post blogs (text) and images that stimulate discussion and the formation of social groups [30]. The effects of these networks on behavioral change have been evaluated with inconsistent effects found with respect to diet and exercise [31], but to date, the effectiveness of social networks in reducing alcohol consumption has not been determined [30,31], but it is currently being trialed in youth with depression and who engage in binge drinking [32]. In contrast, the persuasive effects of Web-based social networks have been extensively harnessed by alcohol brands to engage with alcohol consumers, with some brands having attracted millions of followers [33,34]. This trial will evaluate the effectiveness of the online coaching component of Hello Sunday Morning’s *Daybreak* program and associated support as a means of reducing alcohol consumption.

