## Discussion

To the best of our knowledge, this will be the first formal evaluation of the effectiveness of a smartphone-based peer support platform with coaching in reducing alcohol consumption and associated harms. It will assess critical, clinically relevant outcomes, including changes in alcohol consumption and improvements in mental health and quality of life. The minimal use of incentives in the project design will mean that the findings will be generalizable to real-world settings, with the long period of follow-up important in establishing the persistence of any behavioral changes.

Currently, there is no definitive evidence to support the effectiveness of standard brief interventions among those with more severe alcohol disorders, with equivocal findings for both reductions in alcohol use and improving treatment seeking [15]. Nearly half of Hello Sunday Morning participants score in the probable dependence range on the AUDIT [35], so the outcomes for this subgroup of participants is of particular importance in addressing the gap in the provision of effective alcohol consumption interventions.

The study has been powered to detect effects within critical subgroups, namely, those with people with potential alcohol dependence and by gender. Therefore, in addition to reporting statistical significance results for the main analyses, which may represent trivial changes given the overall size of the sample, we will report effect sizes and discuss effects in terms of their clinical significance, eg, changes in categorical levels on the K-10 and AUDIT.

With respect to the continuing provision of the service, *Daybreak* is a service of the organization Hello Sunday Morning, which is funded through a range of commercial and corporate partnerships, grants, and government contracts. These will allow ongoing dissemination of the service including hosting the program and funding its health coaches. If successful, outcomes of the study will be used to advocate for further funding and wider dissemination via other sites, such as general practitioners and hospital emergency departments.

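### Sixty per group does not give 80% power for d=0.2 at 6 months (about 14-24%), so the statement that the study is powered within subgroups fails at its own design effect

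*Protocol article*

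**What the plan says.** The Sample Size section of the protocol article (the text continues after Figure 1) sets the design effect: "On the basis of a small estimated effect size of *f=* 0.10 (equivalent an effect size of *d*=0.2) at 6 months". Its other inputs are an assumed correlation of 0.5 among the assessments and a 5% significance level. From these it states that "we will require 60 people per group for the main analysis based on power of 0.80". It names no test or formula.

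The 60 then becomes the target for the smallest subgroup cell, males with probable dependence. With 50% of users expected to be probably dependent and 40% male, this leads to 300 per arm, and with 35% attrition to 467 per arm.

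The Discussion relies on this: "The study has been powered to detect effects within critical subgroups", and it names probable dependence and gender as those subgroups. The Analysis section assesses the intervention by a time-by-group interaction in a mixed model. Assessments are at baseline and 1, 3 and 6 months.

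**The concern.** For two groups at one time point, f=0.10 and d=0.2 are indeed the same effect, but detecting it takes several hundred per group, not 60. A number near 60 is typical of a repeated-measures interaction calculation, in which f is defined differently and f=0.10 is a much larger 6-month difference. The section appears to use one definition for the effect and another for the sample size.

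This matters because the 60 fixes the whole recruitment target and supports the subgroup claim. The Discussion treats the probable-dependence subgroup as particularly important. If a null result there is read against a claim of adequate power, it will be taken as evidence that coaching does not help these participants, when the trial had about an even chance or less of detecting the design effect.

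**Working it through.** **Inputs, all from the protocol article.** f=0.10, stated as d=0.2 at 6 months; r=0.5; power 0.80; alpha .05; 60 per group; shares 50% and 40%; attrition 35% (Sample Size). Two groups (Design). Four assessments (Abstract, Table 1). Time-by-group test (Analysis). *Assumptions:* two-sided test, equal correlation of 0.5 between all assessments.

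**1. Trying to reproduce 60.** For the repeated-measures interaction, λ = f²·N·m/(1−r), with df (k−1)(m−1) and (N−k)(m−1).
- k=2, m=4, N=120: λ = 0.01×120×4/0.5 = 9.6 on 3 and 354 df; power 74%.
- 80% is first reached at N=138, which is 69 per group.
- Values near 60 need inputs that are not this trial's: five assessments (61 per group), or three groups with four assessments (58).
- The between-group version needs 247 per group.

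The stated figure is not reproduced from the documented design.

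**2. What f=0.10 means in that formula.** With two groups, the interaction f is half the SD, across the four assessments, of the standardised between-group differences.
- Differences (0, 0, 0, 0.2): mean 0.05; mean square deviation (3×0.0025+0.0225)/4 = 0.0075; SD 0.0866; f = 0.0433. The pattern (0, 0.2, 0.2, 0.2) gives the same f.
- So f=0.10 corresponds to d = 0.2×0.10/0.0433 = 0.46 for these patterns.
- If the effect grows to 0.2 at 6 months, f is 0.0382 (linear in months) or 0.0373 (equal steps per visit).

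**3. Power at 60 per group for d=0.2 at 6 months.**
- Two-sample t test, noncentrality d/√(2v/n). For 6-month values v=1, and for change scores v=2(1−r)=1: 0.2/√(2/60) = 1.095; power 19%.
- Baseline-adjusted, v=1−r²=0.75: noncentrality 1.265; power 24%.
- 3-df time-by-group test: λ = 0.0433²×960 = 1.8; power 17.5%. With a growing effect λ is 1.4 or 1.33; power about 14%.

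**4. Size needed for 80%.** The normal approximation 2v(1.96+0.842)²/0.2² gives 393 (v=1) and 295 (v=0.75); the exact t gives 394 and 296. The 3-df test needs 365 per group (effect at 6 months only, or constant over follow-up), 468 (linear in months) or 492 (equal steps).

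**5. Subgroups.** The later arithmetic is sound: 300×0.5×0.4 = 60, and 300/0.65 = 462 against the stated 467. With 300 completers per arm, power at d=0.2 and the d detectable with 80% power (exact t) are:

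| Subgroup | n per arm | Power, unadjusted / adjusted | Detectable d, unadjusted / adjusted |
|---|---|---|---|
| Male and dependent | 60 | 19% / 24% | 0.516 / 0.447 |
| Male | 120 | 34% / 43% | 0.363 / 0.314 |
| Probable dependence | 150 | 41% / 51% | 0.325 / 0.281 |
| Female | 180 | 47% / 59% | 0.296 / 0.256 |

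**6. Full sample.** 467×0.65 ≈ 304 completers per arm. Power at d=0.2 is 69% on a 6-month change-score contrast and 81% baseline-adjusted. The 3-df test has 72% power if the effect is at 6 months only or constant, and 57% to just under 60% for the two growing patterns.

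**The case against.** **It is a repeated-measures calculation, so a single-time-point check is unfair.** That such a formula was used is an inference, since the article names no method. Even if it was, the documented design needs 69 per group, and f=0.10 is then not d=0.2. More generous readings also fall short: a one-sided test gives 29-35% at 60 per group, and averaging all three follow-ups with baseline adjustment gives 39%, although that is no longer the stated 6-month effect.

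**The 60-person cell is not what the Discussion names.** This stands. The Discussion refers to dependence and gender, which are single-factor groups. A reader might infer that every subgroup has about a one-in-five chance of detecting d=0.2. The documents do not support that: it holds for the male-and-dependent cell, while the single-factor groups have 34-59%. All remain below 80%.

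**Other statements should not be drawn in.** A reader might go further on three points, none of which is shown to be an error.
- The Discussion's caution that significant results are ones "which may represent trivial changes given the overall size of the sample" is defensible. At 304 per arm the smallest significant observed d is about 1.96×√(2/304) = 0.16, or 0.14 with baseline adjustment, which is below the design effect.
- The Abstract's "We will recruit 467 people per group to detect an effect size of" f=0.10 is not shown to be wrong. With d=0.2, about 304 completers give 81% power under a baseline-adjusted 6-month contrast.
- The Introduction's report that "a comparison of alcohol interventions found no significant difference between guided" and unguided interventions (g=0.23 and 0.20) does not discredit d=0.2. These are separate pooled effects, the article itself notes the small number of guided studies, and d=0.2 was set below the cited 0.3-0.4.

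**Conclusion.** The point holds in two parts. First, the statement that 60 per group gives 80% power is wrong for the stated effect: power is about 14-24%, and the size needed is roughly five to eight times larger (296/60 = 4.9; 492/60 = 8.2). It is also short on the most plausible method behind it (74% at 60; 69 needed). Second, the statement of power within subgroups fails at d=0.2, since no named subgroup exceeds 59%. If the secondary hypotheses are tested as differences in the coaching effect between subgroups, power is lower still. The subgroup claim could hold for larger effects, but the article sets no such effect.

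The results assume a two-sided 5% test, equal correlation of 0.5 between assessments, and the expected subgroup shares and attrition. A reader might infer that the trial as a whole is far too small; the figures do not support that. Full-sample power is 57-72% for the planned test and 81% under a baseline-adjusted contrast, so the full-sample comparison is much less affected than the subgroups.

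**What to change.** Keep recruitment at 467 per arm and change the text:

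1. In Sample Size, remove the statement that 60 per group gives 80% power. Deleting only the reference to the main analysis would leave the wrong figure in place. State one definition of the effect: either d=0.2 between groups at 6 months, or an interaction f with the time pattern it assumes.
2. State full-sample power at about 304 completers per arm for the planned time-by-group test: 72% if d=0.2 appears only at 6 months or is constant over follow-up, about 57% to just under 60% if it grows gradually, and 69% on a 6-month change-score contrast. Quote 81% only if a baseline-adjusted 6-month contrast is adopted as the primary analysis, which the Analysis section does not currently plan.
3. In the Discussion, replace the subgroup-power sentence with the subgroup power above and the detectable effects (d of about 0.45-0.52 in the 60-per-arm cell, about 0.26-0.36 in the single-factor subgroups), and describe subgroup results as exploratory.

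The cost is rewording; no participants are added, and the article reports that analysis has not begun. The downside is that the stated subgroup and full-sample power become less favourable.

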### Outcome Measures

All measures will be assessed at each time point except the AUDIT (baseline only) and adverse events [47] (baseline and the final time point; see Table 1). The primary outcome will be change in AUDIT-consumption (AUDIT-C) scores. The AUDIT was developed by the World Health Organization and validated in a range of countries, including Australia [44]. It has a range of 0-40: a threshold of 8 or more will be used as a screening measure to identify eligible participants at baseline. With follow-up at 1, 3, and 6 months, the change in the first 3 questions (known as the AUDIT-C) will be the primary outcome and used to assess change in alcohol use (as some of the other AUDIT questions use a reference period of the last 12 months). The AUDIT-C has also been shown to predict clinical outcomes at 1 year [48]. The secondary outcomes will be changes in:

Alcohol consumption assessed with a 7-day drinking-diary [49,50].Kessler’s K-10 is a brief screening instrument for psychological distress and also a treatment outcome measure [51]. Scores range from 10 to 50, with scores of 20-24 interpreted as showing a mild distress, 25-29 a moderate distress, and 30-50 showing a severe mental health distress.Kessler’s Days out of role [52] will be used to quantify days either completely or partially out of role in the previous 30 days and the number of these due to alcohol use. Those with alcohol dependence have significantly more days completely or partially out of role than those without a disorder. Similarly, those with comorbid substance use and anxiety disorders or substance, anxiety, and affective disorders have increased days out of role [52].Health resource use will be assessed with a checklist of medical and other health professionals consulted in the last 8 weeks and adapted from an existing checklist [53] to include alcohol or other drug treatment services and alcohol pharmacotherapy.The global rating item from the Pittsburgh Sleep Quality Index will be used to categories sleep quality on a 4-point scale (very bad-very good) in the previous month [54].The 3-item Godin Leisure-Time Exercise questionnaire will be used to quantify the frequency of spending 15 minutes or more engaged in each of 3 levels of exercise intensity (strenuous, moderate, and light) in the last 7 days [55].Quality of life will be assessed with the 8-item EUROHIS-QoL that has been validated in Australia [56] and is recommended for use in alcohol and other drug treatment services [57].Adverse events associated with alcohol use will be assessed at baseline and 6 months with the checklist from the Core alcohol and drug survey [47]. It was designed specifically for college populations, so 2 items specially referencing this setting were modified (ie, “missed a class” changed to “missed a class or work” and “been in trouble with police, resident hall, or other college authorities” changed to “been in trouble with police or other authorities”). Given the focus on alcohol, we deleted the reference to drug use from the lead in statement and from 1 item (“Thought I might have a drinking or other drug problem”). Among college students in the United States in the previous 12 months, more than one-third reported driving under the influence and 20%-30% had been in an argument or fight.

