## Methods

### Design

We will use a randomized control design to compare (1) the *Daybreak* program including peer support, behavioral experiments plus online coaching or (2) *Daybreak* program including peer support and behavioral experiments. (The content of the interventions are described below.) Outcome data will be collected at 1, 3, and 6 months post enrollment in the study with all groups receiving the same schedule of assessments (Figure 1). Australian ethical guidelines preclude the use of placebo (no treatment) control groups where a risk has been identified and there are existing treatments/interventions [43].

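### The 8-week service-use recall at the 1-month survey reaches back before enrolment, and the unstated recall of the CORE harms checklist may do the same at 6 months, diluting secondary outcomes

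*Protocol article*

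**What the plan says.** **Service use.** Outcome Measures fixes the recall: "Health resource use will be assessed with a checklist of medical and other health professionals consulted in the last 8 weeks". The checklist was extended to cover alcohol and drug treatment services and alcohol pharmacotherapy. The Design section says "Outcome data will be collected at 1, 3, and 6 months post enrollment in the study", and Outcome Measures adds "All measures will be assessed at each time point except the AUDIT (baseline only) and adverse events". Table 1 confirms that service use is asked at baseline and at 1, 3 and 6 months. The Analysis section then uses specialist alcohol services or pharmacotherapy as a covariate in a sensitivity analysis.

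**Alcohol-related harms.** "Adverse events associated with alcohol use will be assessed at baseline and 6 months with the checklist from the Core alcohol and drug survey". The adaptations are listed: two items that referred to a college setting were reworded, and "we deleted the reference to drug use from the lead in statement and from 1 item". No recall period for trial participants is given. The paragraph ends with results from another population: "Among college students in the United States in the previous 12 months, more than one-third reported driving under the influence".

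**The protocol's own reasoning on recall.** AUDIT-C, not the full AUDIT, is the follow-up outcome, "as some of the other AUDIT questions use a reference period of the last 12 months".

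Under Analysis, the intervention effect on each primary and secondary measure is a time-by-group interaction.

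**The concern.** A follow-up question that looks back past randomisation counts events that the intervention could not have influenced. Those events are equal in the two arms in expectation, so they pull the arms together. The same events can also be reported at baseline and again at follow-up, which blunts a measure of change.

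The protocol recognises this for the AUDIT and avoids it there. It does not say whether the same problem was considered for the CORE checklist, and it sets an 8-week window at a 1-month survey. Alcohol-related harms are named as a secondary outcome in the abstract and are measured only at baseline and 6 months, so no other wave can make up for a diluted 6-month answer. For the sensitivity analysis the problem is different: if the 1-month value is used, treatment received before the trial can be classed as treatment during it.

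**Working it through.** The protocol gives no overlap or dilution figure, so there is none to reproduce.

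**Inputs from the protocol:** service-use recall of 8 weeks = 56 days; surveys at 1, 3 and 6 months; CORE at baseline and 6 months; 467 recruited per arm with 35% lost, so 467 × 0.65 = 303.55, about 304 per arm.

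**Assumptions:** 1 month = 365.25/12 = 30.44 days (28 days as an alternative); CORE recall of 12 months (not stated); constant event rate; effect starting at randomisation; true rate ratio 0.70 or 0.80.

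**Step 1: share of the window before enrolment** = max(0, window − time since enrolment) / window.

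| Measure and survey | Calculation | Share |
|---|---|---|
| Service use, 1 month | (56 − 30.44)/56 = 25.6/56 | 46% |
| Service use, 1 month taken as 28 days | (56 − 28)/56 | 50% |
| Service use, 3 months (91 days) | window shorter than follow-up | 0% |
| Service use, 6 months (183 days) | window shorter than follow-up | 0% |
| CORE, 6 months, if recall is 12 months | (365.25 − 182.6)/365.25 | 50% |
| CORE, 6 months, if recall is 6 months or less | window no longer than follow-up | 0% |

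**Step 2: rate ratio that would be observed** = share + (1 − share) × true ratio.

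- Service use at 1 month: 0.456 + 0.544 × 0.70 = 0.84; with 0.80 it is 0.89.
- CORE under 12-month recall: 0.5 + 0.5 × 0.70 = 0.85; with 0.80 it is 0.90.

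For counts the expected absolute difference is unchanged, because both arms gain the same number of earlier events. The relative effect shrinks by about half.

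**Step 3: a yes/no harm item, as illustration.** Assume a 12-month prevalence *p* in the control arm and a hazard ratio of 0.70 after randomisation. With h = −ln(1 − p), the 6-month risks are 1 − exp(−0.5h) and 1 − exp(−0.5h × 0.70). The 12-month risks are p and 1 − exp(−h(0.5 + 0.5 × 0.70)).

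| p | 6-month window | Risk ratio | Power | 12-month window | Risk ratio | Power |
|---|---|---|---|---|---|---|
| 0.20 | 10.6% vs 7.5% | 0.71 | 26% | 20.0% vs 17.3% | 0.86 | 14% |
| 0.35 | 19.4% vs 14.0% | 0.72 | 43% | 35.0% vs 30.7% | 0.88 | 21% |

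Power is for two proportions at follow-up with 304 per arm. It does not model the planned time-by-group interaction, so only the direction and rough size carry over.

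**Step 4: coverage of follow-up by the service-use windows.** The present windows cover 30.4 + 56 + 56 = 142 of 183 days after enrolment (78%). Four weeks at every wave would cover 3 × 28 = 84 days (46%). Shortening only the 1-month window keeps 28 + 56 + 56 = 140 days (77%), or 142 days if it asks about the time since enrolment.

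**The case against.** The strongest objection concerns CORE. A reader might infer that the trial's checklist has a 12-month recall as a matter of record. The protocol does not say so. The 12-month phrase describes published results in US college students, the list of edits is not declared complete, and exact item wording is something that an article can leave to the full protocol. This stands, and the CORE part must stay conditional. The inference is still a strong one: the authors edited the lead-in, described that edit and mentioned no change of period.

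Three further readings go too far:

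- That the service-use problem affects all of follow-up. It is confined to the 1-month survey.
- That CORE is the only secondary outcome touching on problems. Days out of role due to alcohol also does. Its recall is 30 days and it is asked at every wave, so its window does not reach back before enrolment.
- That a well-powered harms comparison is being lost. The protocol gives no expected effect on harms, and under the ratio assumed above power is low even with a 6-month window.

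It is also fair to say that earlier events are balanced by randomisation in expectation, so they favour neither arm, and that nothing shows AUDIT-C to be affected. Finally, no consequence for the sensitivity analysis has been quantified; the point there is possible misclassification, and only if the 1-month value is used.

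**Conclusion.** The service-use point holds on stated text. At the 1-month survey 46% to 50% of the window precedes enrolment, so a true rate ratio of 0.70 would appear as about 0.84, and pre-trial treatment can enter the sensitivity covariate.

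The CORE point holds conditionally. The recall period is not stated; if the 12 months cited for the reference population was kept, half of the 6-month window is pre-randomisation time and 0.70 would appear as about 0.85. If the recall is 6 months or less, the problem disappears. The overlap shares follow from dates alone. The size of the dilution rests on the assumed ratio, a constant rate and an effect that starts at randomisation.

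The consequence is weaker secondary outcomes, not bias between arms. It is worth correcting because the protocol applies the same reasoning to the AUDIT and the survey edit is small.

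**What to change.** 1. **CORE checklist.** State the recall period. Unless it is already 6 months or shorter, set the lead-in to the past 6 months at the 6-month survey, and at baseline for new enrolees.
2. **Service use.** At the 1-month survey only, ask about the time since enrolment or the past 4 weeks. Alternatively, keep the question and leave the 1-month value out of the effect estimate and the covariate. Keep 8 weeks at 3 and 6 months, where there is no overlap and a shorter window would lose coverage.
3. **Analysis.** Record the wording version for each response. Where baseline and follow-up windows differ, compare arms at follow-up with adjustment for baseline, since a raw change would mix windows of different length. If service use is modelled as a count across waves, allow for window length with an offset.

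**Cost.** Two small edits to online surveys. Enrolment began in February 2018, so two versions will coexist and some participants will have a baseline window that differs from their follow-up window. Comparability with published 12-month figures is reduced. The 1-month service-use answer would cover a shorter period than those at the other waves.
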